### Study-aim and procedure

Our study aims to examine health-related effects from two slightly different live workshops with office workers. Therefore, we contact health counselors at various companies in Germany. If they are interested in participating in our study, further details will be discussed and the employee council and management level will be involved. If the management approves our study, the health counselors will be interviewed and will help to distribute the information among the employees (i.e. via email). In an email, participation in one of our groups will be clearly explained. The study information and the consent form are attached to this email, with additional contact details of the study supervisors (i.e. regarding upcoming questions). As a prerequisite for participation, these documents must be signed and returned. The participants have the opportunity to choose a suitable date from a list of workshop dates in their company. Each participant receives a link to participate in the online questionnaire as well as an activity diary one week before their first workshop. Additionally, we use accelerometers to objectively measure physical activity during this week. Accelerometers with instructions, activity diaries and an online survey will be sent to all consenting participants for data collection. The instructions explain how to attach the accelerometer to the participant’s thigh and hip. Previous studies have indicated three days are sufficient to observe a stable pattern of physical activity [39]. Not wearing the accelerometer for 3 successive days leads to exclusion of the participant from the study.

This procedure is repeated one week before the refresher workshop and after six months. We have no blinding of our workshop supervisors and outcome assessors or data analysts. In each group data collection starts one week before the first workshop. The study procedure is presented in Fig. 1.

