#### Activity tracker

Physical activity is objectively measured by ActivPAL™ (PAL Technologies), which is a validated and reliable accelerometer for activities like sitting, standing, or walking [45, 46]. Especially in sedentary behavior, the ActivPAL™ is a precise and sensitive measurement tool [47]. The sensor is attached to the right thigh and measures not only the number of steps but also various activity patterns. In this study, the measurement is performed over seven consecutive days to examine the average physical activity and to have a comparative value to the PAD.

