### Statistics

All data are processed to enhance quality; for example, in case of missing data, we conduct a missing value analysis (MVA) with a subsequent imputation procedure. Outliers are checked manually. Then, it is planned to perform analyses for repeated measurements of physical wellbeing, HAPA subscales, and the results from the physical activity diary. Results from the Nordic Musculoskeletal Questionnaire are analyzed descriptively. For all analyses, the significance level is set to 0.05.

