## Discussion

We introduced a workshop to increase health-seeking behaviors in office workplaces in Germany. Our workshop is based on a combination of physical activity and health behavior planning.

At first, we want to indicate one minor limitation regarding our data acquisition: we have to validate our PAD. The diary is adapted to a validated questionnaire; however, that questionnaire has not been validated for daily usage. Moreover, the literature showed differences between self-reported (i.e. by questionnaires) and accelerometer-measured physical activity [48, 49]. Therefore, we use accelerometer-measured physical activity to prove our PAD in a sub-sample of our participants. If the result of our analysis shows insufficient validity, only the data from the accelerometry will be used. Another limitation refers to the recruitment process. The participants are recruited in different organizations and therefore have different pre-conditions (i.e. workplace equipment, health services) as well as differently effective health counsellors. Thus, we will collect data on the organization to control for potential experimenter effects between organizations.

In addition, there is some risk of inter-subject group bias if individuals in one group inform a member of the other group about reminders. In the follow-up survey, we will ask the group without reminders whether they received information about the procedure in the other group. We can then perform analyses according to whether participants received information about the other group and exclude them from the analyses, where necessary. Participants of the workshops might be less active in winter. Hence, the season could affect the amount of physical activity. As data of both intervention groups will be collected in the same season, they remain comparable. All these issues could affect our results and should be critically reviewed later.

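### The accelerometer non-wear rule counts successive days although its rationale is a number of days, has two readings, and removes participants from the whole study instead of from the accelerometer data

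*Protocol article*

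**What the plan says.** All references are to the protocol article.

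- **Study-aim and procedure**, rationale: "Previous studies have indicated three days are sufficient to observe a stable pattern of physical activity".
- **Study-aim and procedure**, the rule that follows at once: "Not wearing the accelerometer for 3 successive days leads to exclusion of the participant from the study".
- **Activity tracker**, length of a measurement: "the measurement is performed over seven consecutive days to examine the average physical activity".
- **Study-aim and procedure**, repetition: "This procedure is repeated one week before the refresher workshop and after six months". With the baseline week this makes three waves.
- **Study-aim and procedure**, who receives the device: "Accelerometers with instructions, activity diaries and an online survey will be sent to all consenting participants for data collection". The Discussion describes a narrower use: "we use accelerometer-measured physical activity to prove our PAD in a sub-sample of our participants".
- **Statistics**, outcomes to be analysed: "it is planned to perform analyses for repeated measurements of physical wellbeing, HAPA subscales, and the results from the physical activity diary". Accelerometry is not in this list. The same section plans a missing value analysis followed by imputation.

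**The concern.** The rationale concerns how many days are observed. The rule concerns whether days are adjacent. These differ, so the rule can discard weeks that the protocol's own reasoning would accept. The sentence also has two meanings, and they give different exclusions. That matters for a rule which staff apply unblinded: the protocol states that supervisors, outcome assessors and data analysts are not blinded.

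The consequence matters more than the day count. A poor accelerometer week is a missing value for one instrument at one wave. The rule treats it as a reason to remove the person altogether. By the second and third waves, participants have been allocated and reminders have been sent to one group. Removing people then means that the groups analysed are no longer the groups formed by randomisation, and valid questionnaire and diary data are lost as well.

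**Working it through.** **Inputs.** Seven days per measurement (Activity tracker); three days regarded as enough, and three successive days in the rule (Study-aim and procedure). The plan attaches no figure of its own to this rule, so there is nothing to reproduce. The planned sample size of 168 does not enter the check.

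**Two readings.** W is a worn day and N a day not worn.

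- Reading A: a run of three or more N days leads to exclusion.
- Reading B: not reaching a run of three W days leads to exclusion.

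**All patterns.** There are 2^7 = 128 possible weeks. With at least three worn days: C(7,3) + C(7,4) + C(7,5) + C(7,6) + C(7,7) = 35 + 35 + 21 + 7 + 1 = 99. With fewer than three: 1 + 7 + 21 = 29.

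| Worn days | Patterns | Excluded, A | Excluded, B |
|---|---|---|---|
| 0 | 1 | 1 | 1 |
| 1 | 7 | 7 | 7 |
| 2 | 21 | 18 | 21 |
| 3 | 35 | 16 | 30 |
| 4 | 35 | 5 | 19 |
| 5 | 21 | 0 | 3 |
| 6 | 7 | 0 | 0 |
| 7 | 1 | 0 | 0 |

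**How the key cells arise.**

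- A, four worn days: the three N days must form one block, which can start on day 1, 2, 3, 4 or 5. That gives 5.
- A, three worn days: four N days fall into the four spaces around the worn days. All four together: 4 ways. Three together and one elsewhere: 4 × 3 = 12. Total 16.
- A, two worn days kept: five N days fall into three spaces with at most two in each, so 2, 2 and 1 in some order. That gives 3 kept and 21 − 3 = 18 excluded.
- B, three worn days: only 5 of the 35 patterns have the three days together, so 35 − 5 = 30 are excluded.
- B, four worn days: a run of at least three occurs in 4 + 12 = 16 patterns, so 35 − 16 = 19 are excluded.
- B, five worn days: excluded only if no run exceeds two, so 2, 2 and 1 in some order. That gives 3.

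**Totals among the 99 patterns with at least three worn days.** A excludes 16 + 5 = 21. B excludes 30 + 19 + 3 = 52. Among the 29 patterns with fewer than three, A keeps 3 and B keeps none.

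**One week that fails both readings.** W W N N N W W has four worn days, a three-day gap, and no three successive worn days.

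**Scope of the penalty.** The exclusion is from the study. The planned repeated-measures analyses cover wellbeing, the HAPA subscales and the diary. None of these needs a worn accelerometer to be valid. The same section intends to impute missing data, yet here a missing-data problem is met by removing the person. If accelerometry is used only in a sub-sample to check the diary, as the Discussion has it, removal from the whole study is harder still to justify.

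**The case against.** **The three-day statement is not a formal minimum.** A reader might infer that the rule contradicts a three-day criterion. The text does not go that far. It reports that three days were sufficient in earlier studies and sets no minimum number of valid days. A rule stricter than a cited sufficiency result is poorly matched to it, but is not a contradiction. This stands.

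**Keeping two-day wearers depends on the reading.** A reader might also infer that the plan retains people with only two worn days. That is true only on reading A, and for just 3 patterns. Reading B fits the preceding sentence at least as well and keeps nobody with fewer than three days. This stands too. It does not rescue the rule, because reading B excludes more weeks with at least three worn days (52 against 21).

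**The counts are not frequencies.** Unworn days need not be equally likely or independent, and some patterns require the thigh sensor to be taken off and put back repeatedly. The counts show what the rule permits, not how often it would happen.

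**Differential loss is not shown.** A reader might infer that reminders change device wear and so bias the comparison. The reminders concern physical activity at the workplace, and nothing in the article says that wear would differ between groups. It is a possibility, not a finding.

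**Accelerometry may matter more than the Statistics list suggests.** The abstract names tracker data among the things examined, and the Discussion would rely on accelerometry alone if the diary proves insufficiently valid. That is a fair reason to want good wear data. It does not justify dropping the same person's wellbeing and HAPA scores.

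**Valid-day definitions often sit in an analysis plan.** True, and their absence would be no finding. But this rule is stated, with its consequence.

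**Conclusion.** The point holds in this form: the rule does not match its stated rationale, it has two readings, and its penalty reaches outcomes that do not depend on the device. On either reading a participant with four of seven worn days can be removed from the study, including at the two waves after the first workshop.

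The size is 21 (reading A) or 52 (reading B) of 99 weeks with at least three worn days, counted as possibilities. This rests on a seven-day week and on taking three days as the benchmark that the protocol itself cites. The case against the whole-study penalty needs neither count.

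The number of participants lost cannot be estimated. The article gives no expected non-wear rate, and any percentage would rest on an assumed rate and on independence between waves. It is also not stated whether allocation precedes the baseline week, so only exclusions at the two later waves clearly fall after allocation. The change should be made, but the documents do not show that the trial's conclusions would be altered.

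**What to change.** Replace the rule with text along these lines:

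> An accelerometer assessment is valid if the device was worn on at least three of the seven days, successive or not. If this is not met, only the accelerometer value of that wave is set to missing and handled by the planned missing-value procedure. The participant remains in the study and in all other analyses.

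The threshold of three follows the protocol's own cited rationale. The sponsor should confirm it against that source, which is not available here. The revision should also settle whether all participants or only a sub-sample wear the device, so that it is clear to whom the definition applies.

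The cost is a few sentences and somewhat more missing accelerometer values to handle. No additional data collection is needed.

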## Methods

### Participants

We recruit office desk workers aged between 18 and 67 years from different organizations (i.e. public administration with standard office workplaces) in Germany. Two intervention lines are planned: one live workshop group with and one without reminders. After attending the first workshop participants in the appropriate intervention group will receive reminders via e-mail twice a week. The e-mails remind the participants of the possibilities to be physical active at the work place previously introduced through the workshop. Overall, eight e-mails will be sent until participants answer the second online survey one month after participating in the workshop. We use a randomized allocation of the participants to both groups. As inclusion criteria, we define an age group between 18 and 67 years and the employee council of each institution has to approve the participation. Additionally, participants are asked not to take part in other studies during the time of the workshop intervention. Participants are excluded if they take part in only one workshop or do not fill in the questionnaires (missing answers > 30%) appropriately. All participants will be informed about the content and objectives of our study, they can ask questions, and they can withdraw from the participation at any time. As a prerequisite for participation, participants of our study sign a declaration of consent. A meta-analysis [38] revealed small intervention effects of workplace physical activity interventions (d = 0.21). Based on this assumption, power-analysis (G-Power 3.1) indicated in sum 168 participants for an ANOVA with repeated measures (within-between interaction). Our calculation included *f* = 0.11, *α* = 0.05, β = .80, three groups, and three measurements.

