### Monitoring and ethics

There will be no data monitoring committee. However, data will be regularly monitored (i.e. following each workshop) by the principal investigators. There is no external funding for this study and therefore the principal investigators have no financial or other competing interests. Adverse events during the workshops or within data collection will be logged and reported. The study is approved by the ethics committee of Charité Universitätsmedizin Berlin (No.: EA2/185/19). We have to point out that our ethics approval does not yet cover the implementation of reminders. This aspect is currently being submitted in a supplementary application. We assume that this aspect is ethically acceptable and that a corresponding positive vote can be handed in later. Other protocol amendments are not planned. In case an adjustment to the protocol is necessary, this will be indicated in the subsequent report of our results. By publishing this study protocol in advance as well as by using a study registration, all subsequent changes are traceable. Only the principal investigators of this study will have access to the final datasets. All data will be encoded and stored electronically on a password-protected external drive. All identifiable data (i.e. completed questionnaires) are secured as a single version in lockable cabinets that are in lockable rooms.

Only analyses based on aggregated data (*n* > 15) will be released back to the organization to ensure the anonymity of participants. The invitation to participate in the study will state that participation is voluntary and no negative consequences will impact those that choose not to participate. The overall study results and circumstances will be made available to all individuals irrespective of their group allocation.

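### Analyst blinding is declined without a reason, while a manual outlier check and one discretionary exclusion are left to people who know the allocation

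*Protocol article*

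**What the plan says.** Under Study-aim and procedure, the protocol article says "We have no blinding of our workshop supervisors and outcome assessors or data analysts". It gives no reason.

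Two later steps need judgement:

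- **Outliers.** The Statistics section says "Outliers are checked manually". It names neither a criterion nor the action that follows.
- **Contamination.** The Discussion says "In the follow-up survey, we will ask the group without reminders whether they received information about the procedure in the other group", and continues: "We can then perform analyses according to whether participants received information about the other group and exclude them from the analyses, where necessary". It does not say when exclusion counts as necessary.

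The other exclusions follow stated rules. Under Participants: "Participants are excluded if they take part in only one workshop or do not fill in the questionnaires (missing answers > 30%) appropriately". Under Study-aim and procedure: "Not wearing the accelerometer for 3 successive days leads to exclusion of the participant from the study".

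Monitoring and ethics restricts access to the final datasets to the principal investigators. It says the data are encoded for storage, but not that the group is masked.

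**The concern.** Supervisors who deliver the workshop necessarily know who is in which group. People who clean and analyse the data need not. Once analysts know the arm, any step that depends on their judgement can lean towards the expected result, even without intent.

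The planning effect is small (d = 0.21, Participants section), so a few decisions of this kind can be large relative to what the trial is designed to find.

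The contamination exclusion adds a second problem. Only the group without reminders is asked, so only that group can lose participants by this route, and it loses them after randomisation. Such a one-sided loss can bias the comparison even if the analyst is masked.

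**Working it through.** **1. Group size.** The Participants section gives f = 0.11, α = 0.05, power 0.80 (printed as β), three groups, three measurements and a total of 168. The correlation between measurements and the sphericity correction are not given; 0.5 and 1 are assumed here. For the within-between interaction:

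- λ = f²·N·m/(1 − ρ) = 0.0121 × 168 × 3/0.5 = 12.2
- df₁ = (3 − 1)(3 − 1) = 4; df₂ = (168 − 3)(3 − 1) = 330
- power = 0.803, and 168 is the smallest balanced total that reaches 0.80

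The stated total is reproduced, so 168/3 = 56 per group is a fair basis for illustration. The figure itself is not in dispute.

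**2. Shift from removing values in one arm.** Assume a standard normal outcome, no true effect, and removal of the j lowest of n = 56 values in one arm. The expected shift in SD units is

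shift = −[E(x₍₁₎) + … + E(x₍ⱼ₎)]/(n − j),

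where E(x₍ᵢ₎) is the expected i-th smallest of 56 standard normal values. Numerical integration gives −2.29, −1.91 and −1.68 for i = 1, 2, 3.

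| Removed | Shift (SD) | Share of 0.21 |
|---|---|---|
| 1 | 2.29/55 = 0.04 | 20% |
| 2 | 4.20/54 = 0.08 | 37% |
| 3 | 5.88/53 = 0.11 | 53% |

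**3. Type I error.** Simulation of the same removals with a two-sided two-sample t-test at 0.05 (20,000 to 60,000 runs) gives about 6% for one value removed, 7.4 to 7.9% for two, and 9.9 to 10.2% for three. With nothing removed it is 4.9%.

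**4. Same removal without knowledge of the arm.** Taking the 1, 2 or 3 most extreme values from each end of the pooled data, whichever arm they belong to, gives a mean shift of about 0 and a type I error of about 4.8%. In this model the harm comes from knowing the arm, not from removal as such.

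**5. What a code can and cannot mask.** A neutral code can hide the reminder and no-reminder labels while outcome values are checked. It cannot hide the arm of anyone who answered the contamination question, because only one group receives it. Nor can it fully hide the control group, which according to Study-aim and procedure receives only the pre- and post-study questionnaires.

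**The case against.** The strongest reply is that the text supports less than it seems to. Several stronger readings are tempting and should not be made.

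- **That analysts pick by hand whom to exclude.** Attendance, missing answers and accelerometer wear have fixed rules. Only the contamination exclusion is plainly discretionary. This objection stands.
- **That outliers are deleted.** The protocol says they are checked. The criterion and the action may be set out in an analysis plan that is not shown, so their absence is no fault here. This also stands. But such a plan would not by itself answer the explicit statement that analysts are unblinded.
- **That investigators look at outcomes by arm as data accrue.** Monitoring and ethics says "data will be regularly monitored (i.e. following each workshop) by the principal investigators". It does not say that arms are compared or that anything is decided on that basis, so the point does not rest on it.
- **That coded labels would close the route at no cost.** They would not, for the reasons in step 5 of the working, and someone has to hold the code.
- **That no reader could detect the effect.** The protocol promises to report adjustments and announces the contamination exclusion in advance.

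It is also fair to say that the figures describe the worst case. They assume that exactly the least favourable values go, which an honest outlier check would not do. They use a simple t-test rather than the repeated-measures interaction. The contamination exclusion selects on information received, not on outcome, so the figures do not estimate its effect.

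**Conclusion.** The point holds in a limited form. The lack of analyst blinding is a stated design choice, made without a reason, where masking is feasible. It coincides with two judgement steps: the manual outlier check, and the contamination exclusion confined to the group without reminders.

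The size given, about 0.08 to 0.11 SD and a type I error of about 8 to 10%, is an upper illustration for two or three values removed from one arm. It rests on normal data, no true effect, 56 per arm and a two-sample t-test. It shows that the route is material beside an effect of 0.21. It does not predict what this team would do.

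The contamination exclusion is a separate weakness that masking does not cure. The documents do not allow its size or direction to be estimated. The matter should be corrected, but it does not invalidate the design.

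**What to change.** 1. Replace the group by a neutral code covering all groups, including the control group, in the dataset used for cleaning. An existing team member who does not clean data holds the key.
2. Make and log all outlier and imputation decisions before the code is opened.
3. Delete a value only for a documented recording or device error, and repeat the main analysis with all values kept.
4. Keep all randomised participants in the main analysis irrespective of their answer to the contamination question. Use the exclusion of informed participants only as a sensitivity analysis.

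Items 3 and 4 protect the result even where the data pattern gives the arm away. Sample size, power and significance level do not change. Data Availability says the study has not started, so the cost is protocol wording, a coded variable and one small constraint: the code-holder stays out of data cleaning. As only the principal investigators have access to the final datasets, the protocol should name the role that holds the key.

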### Intervention

The first workshop lasts about two hours, the refresher workshop only one hour. Each workshop consists of active and passive parts. Table 1 describes the first workshop including active and passive parts. The refresher workshop includes some new activities (see part III in Table 1) as well as an interactive question-answer part. In the latter participants can ask questions about the workshop and further individual strategies, and can discuss adaptations. This concept is used in a live workshop with and without reminders. The reminders are used to retain the acquired contents and knowledge of the first workshop and to give incentives for physical activity.

**Table 1 Tab1:** Description of main contents during the workshop; participants were actively (i.e. physically active) or passively involved

***Part***	***Content***	***Participants’ involvement***
I	Workshop trainers give some general information about inactive lifestyle and behavior (i.e. statistics) at German workplaces and resulting health-related issues (i.e. physically, social, psychological), based on recent studies. Different concepts for increased physical activities at the workplace are shown and participants are asked in anonymized live-questions about their daily physical activity.	passive
II	The trainers give instructions on adequate health safety standards regarding the office desk setting, based on German laws and regulations. This includes the rights & duties as well as the health-related behavior of office workers at their workplace (i.e. position of the desk, equipment, sitting/standing positions) in Germany. Again, the participants are asked for their participation in anonymized live-questions about these topics.	passive
III	Trainers show some exercises from the areas of mobilization, strengthening, and stretching. All examples can be performed at the workplace. At the end of this tryout, some recommendations for physical activity (i.e. how long and often exercises should be performed) are given.	active
IV	Trainers and participants of the workshop discuss opportunities and barriers to daily physical activity in individual group activities. Experiences are shared and the group works on the conception of action plans. Finally, each participant should create his/her plan.	active

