#### Nordic musculoskeletal questionnaire (NMQ)

This questionnaire aims to detect musculoskeletal stress in different regions of the body [40]. The NMQ consists of two parts: first, general information about the participant including the individual situation at work, and second, detailed questions about previous and existing physical stress. The latter also examines special regions of the body (i.e. neck, shoulder, lower back). All questions include the duration and frequency of physical stress, especially during the last 12 months and the last seven days. Previous research concluded that the NMQ is sensitive, repeatable, and a useful screening tool [41]. We use this questionnaire in two ways: (i) as a screening tool to adapt the physical activities in our refresher-workshop, and (ii) to record changes in physical stress a few weeks after the workshop.

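### Workshop trainers are left unblinded although they need not know who receives the reminder e-mails, which leaves the 24-week reminder contrast open to avoidable performance bias

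*Protocol article*

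**What the plan says.** On blinding, Methods, Study-aim and procedure says: "We have no blinding of our workshop supervisors and outcome assessors or data analysts". It gives no reason and no compensating measure.

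On what separates the arms, Methods, Participants says: "Two intervention lines are planned: one live workshop group with and one without reminders". The reminders are e-mails: "After attending the first workshop participants in the appropriate intervention group will receive reminders via e-mail twice a week". Their number and end point are also fixed: "Overall, eight e-mails will be sent until participants answer the second online survey one month after participating in the workshop". Methods, Intervention confirms that the workshop itself is common to both arms: "This concept is used in a live workshop with and without reminders".

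On the refresher, which follows the reminder phase, Methods, Intervention says: "The refresher workshop includes some new activities (see part III in Table 1) as well as an interactive question-answer part". Of the question-and-answer part it adds: "In the latter participants can ask questions about the workshop and further individual strategies, and can discuss adaptations". The Nordic questionnaire is used, among other purposes, "as a screening tool to adapt the physical activities in our refresher-workshop".

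The Discussion considers two neighbouring threats: experimenter effects between organizations, and participants of one arm telling the other arm about the reminders. It does not consider trainers treating the two arms differently.

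**The concern.** In most trials of a workshop the trainer cannot be masked, because the trainer delivers the very thing under comparison. That reason does not apply to the reminder comparison in this trial. The randomised difference is delivered by e-mail, outside the sessions, and nothing in the text requires a trainer to know who gets it.

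The trainers nevertheless meet both arms again at a session whose content is partly at their discretion. A trainer who knows the arm might press the reminder arm harder on its plans, or might make up for the missing e-mails in the other arm. Either would enter the 24-week difference between arms and could not be told apart from the reminders at that time point. The hypothesis at stake, in the Introduction, is that reminders improve the health-related effects.

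**Working it through.** **Where the bias could enter**

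1. First workshop: same concept in both arms.
2. Reminder phase: eight e-mails at two per week, 8 / 2 = 4 weeks, ending with the second survey at one month. One arm only.
3. Second measurement: one week before the refresher (Abstract, Methods; Study-aim and procedure). Nothing done at the refresher can affect it.
4. Refresher: both arms, with open questions, individual strategies and exercises adapted to Nordic questionnaire results. People who attend only one workshop are excluded (Participants), so everyone retained in these two arms has been through it.
5. Final measurement: 24 weeks after baseline. This is the only measurement after the refresher, hence the only one exposed to this route.

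**The plan's own sample size, to obtain a group size**

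Inputs from Participants: f = 0.11, α = 0.05, power 0.80 (printed as β), k = 3 groups, m = 3 measurements. Assumed, because not stated: correlation ρ = 0.5 between repeated measures and sphericity (ε = 1).

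- λ = f² × N × m / (1 − ρ) = 0.0121 × 168 × 3 / 0.5 = 12.20
- df1 = (k − 1)(m − 1) = 4; df2 = (N − k)(m − 1) = 165 × 2 = 330
- Power at N = 168 is 0.803; at N = 165 it is 0.795.

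The stated 168 is reproduced. With equal groups (assumed), that is 168 / 3 = 56 per arm.

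**Illustration of what a trainer-induced difference would do**

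Two-sided normal test of two means, SD 1, no true reminder effect, shift b in SD units:

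- SE = √(2 / 56) = 0.189
- False-positive rate = Φ(−1.96 + b / SE) + Φ(−1.96 − b / SE)
- For b = 0.10: b / SE = 0.529, so the rate is Φ(−1.431) + Φ(−2.489) = 0.076 + 0.006 = 0.083.

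| Assumed shift b (SD) | False-positive rate |
|---|---|
| 0 | 5.0% |
| 0.05 | 5.8% |
| 0.10 | 8.3% |
| 0.15 | 12.5% |
| 0.21 | 19.9% |

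Every value of b is an assumption; the documents give no trainer effect. The last row equals the whole effect, d = 0.21, that the plan takes from a meta-analysis of workplace interventions. A shift against the reminder arm would instead hide a real benefit: a true difference of 0.21 SD with a compensating 0.10 SD would appear as 0.21 − 0.10 = 0.11 SD.

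**The case against.** The protocol discloses the lack of blinding openly and contradicts itself nowhere on this point. Unblinded delivery is usual in behavioural trials. The sentence does not say that trainers hold the allocation list, and the custody of that list is a detail that a condensed article often leaves to the full protocol. Participants know whether they receive e-mails and may say so in a session meant for questions, so masking could break down.

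Part of this stands. Masking would be incomplete, and equating supervisors with the trainers of Table 1 is a reading, though the natural one. But the article does more than stay silent: it states that there is no blinding, and it offers no safeguard against differential treatment by arm.

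Three stronger inferences are tempting and are not supported.

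- A reader might infer that the reminder comparison as a whole is compromised. It is not: the measurement one week before the refresher comes directly after the reminder phase and is free of this route.
- A reader might take the higher rows of the table as the likely size of the bias. A shift near 0.2 SD would mean that unintended differences within a one-hour refresher match almost the full effect of a typical workplace intervention. Nothing in the documents suggests that.
- A reader might infer that whole sessions will be run differently by arm. The article does not say whether sessions mix the arms. Participants choose a date in their own company and groups are small (n < 11), which settles nothing.

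**Conclusion.** The point holds as an avoidable risk of performance bias, confined to the 24-week contrast between the two workshop arms. It does not concern the comparison with the questionnaire-only control group.

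Its direction is open and its size cannot be derived from the documents. The figure of about 8% instead of 5% is an illustration that rests on 56 per arm, no true effect and an assumed 0.1 SD difference, a little under half of the planned d (0.10 / 0.21 = 0.48). The risk is larger if sessions are arm-specific, since a whole session could then be run differently. It is limited to individual advice if sessions mix the arms. The priority is low, but the remedy is cheap and the Data Availability statement says that the study has not yet started.

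**What to change.** Change the blinding statement in Study-aim and procedure so that:

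- an existing team member who does not lead the participant's workshops holds the allocation list and schedules the reminder e-mails;
- trainers are not told the arm of any participant or session until the 24-week data are collected;
- any unmasking of a trainer is recorded.

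Do not ask participants during a session to keep quiet about e-mails. In a mixed session this would tell the other arm that reminders exist, which is the contamination that the Discussion itself names and for which it foresees possible exclusions.

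The cost is organisational: one team member must be kept apart from delivery, in a study without external funding. Masking will be partial because participants may reveal their arm. The sample size stays at 168, and the visits and the workshop content do not change.
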